**Abstract**

**Background**

Emergence, of resistance to anti-malarials is a major challenge for effective malaria control in sub-Saharan Africa. Extensive use of chloroquine (CQ) as a monotherapy led to significant increase in levels of resistance across many malaria-endemic countries, including Ethiopia. Thus continuous and regular monitoring of drug efficacy is critical for establishing rational anti-malarial drug policies. This study therefore, assesses the therapeutic efficacy of Chloroquine(CQ) for the treatment of *Plasmodium vivax* infectionsin Northwestern, Ethiopia. **Methods**

An observational, prospective 28-days in vivo therapeutic efficacy evaluation will be conducted from July to December, 2014, in Northwest Ethiopia at Bullen health center. Patients confirmed to have monoinfection of vivax malaria, aged above 6 months will be enrolled. All subjects will be then treated with standard Chloroquine(25 mg/kg for three (3) days). Parasitological and clinical outcomes of treated patients will be evaluated prospectively on days 1, 2, 3, 7, 14, 21, and 28 during the entire follow-up period.. Data will be entered and analyzed using SPSS version 20. Kaplan-Meier survival estimate will be used to analyze therapeutic failure rate during follow-up period. The initial study endpoint will be taken as the risk of failure at 28 days by survival analysis. Changes in fever and parasite clearance will be evaluated at each follow up visit. Changes in mean haemoglobin concentrations will be computed on days 0 and 28 and quantitative variables will be compared using paired *t* test. P value of < 0.05 will be considered a significant level.

**Keywords**

Chloroquine, Efficacy, *vivax malaria*

**Introduction**

There are five species of plasmodia known to infect humans of which, *Plasmodium vivax* is the most widely distributed species responsible for 25-40% of malaria cases worldwide [1], and substantial morbidity associated with vivax malaria has been reported [2-4]. In Ethiopia, vivax malaria accounts for approximately 40% of all malaria cases, and most recently it seems, this proportion is even rising. Despite the public health importance, *P. vivax* malaria has received little attention and limited funds for research and control, since it usually produces less severe symptoms than falciparum malaria [2, 5, 6].

The current treatment for vivax malaria relies primarily upon two anti-malarial drugs, chloroquine (CQ) and primaquine (PQ), with the latter being the only effective drug against the hypnozoite stage. In areas where susceptibility to CQ is ascertained the recommended doses are CQ 25 mg/kg bw (body weight) during three consecutive days (10, 10 and 5 mg/kg bw) and Premaquine(PQ) at 0.25–0.75 mg/kg bw during 14 days [7,8]. Of course, the 14-day treatment effectively cures primary blood infections and is the most effective for preventing relapses [9]. However, in areas where CQR is substantial, it is recommended that artemisinin combination therapy (ACT) be used instead, also in combination with PQ for radical cure [8].

The first evidence of CQ resistant (CQR) to *P. vivax* began to emerge in 1989 [10, 11], 30 years after the documentation of CQR *Plasmodium falciparum*. Since, then the problem of CQR to *plasmodium vivax* continued to occur in different regions at varying degrees. For instance, in Indonesia, East Timor and Papua New Guinea, CQ-resistant vivax malaria has already reached an alarming prevalence [12]. CQR has also occurred in Latin American countries such as (Guyana, Peru and Brazil) [13]. The four clinical trials carried out in Asia (Thailand and Pakistan) and Africa (Ethiopia), for instance, showed that CQ alone (25 mg/kg over 3 days) is less effective against *P. vivax* asexual blood stages than CQ (25 mg/kg over 3 days) co-administered with PQ (15 mg of PQ base/day for 14 days) over 28 days of follow-up [14].

The emergence of resistance to anti malarials threatens efforts towards malaria control and elimination. Resistance to Drugs has been implicated in the spread of malaria to new areas and re-emergence of malaria in areas where the disease had been eliminated. It also plays significant role in the occurrence and severity of epidemics in some parts of the world [15] and results in an ongoing diseases transmission. Therefore, there is a need to monitor, the status of drug resistance to anti-malarials on continuous and regular basis (often at 2 years interval. To do so, three main tools are used for drug resistance monitoring and assessing which includes therapeutic efficacy tests (*In* vivo*)*, in vitro tests, and analyses of molecular markers.

Therapeutic efficacy assessment according to the standard protocol of the WHO is the most useful for updating national treatment policies. These include, therapeutic assessment based on evaluation of the clinical and parasitological outcomes remains the mainstay of monitoring the efficacies of anti-malarial regimens and is recommended [16]. Measures such as parasite clearance time, fever clearance time or gametocyte clearance time in vivo and in vitro assays are used to indirectly detect any variation in parasite sensitivity thereby facilitating early warning in case of emergence of tolerance or resistance [17, 18].

In Ethiopia, Chloroquine 150 mg base tablet *OR* chloroquine syrup 50 mg base is the first line drug of choice for the treatment of vivax malaria. The ideal dose is 10 mg base/kg po immediately (Day 1), followed by 10 mg base/kg po at 24 hours (Day 2), and 5mg base/kg po at 48 hours (Day 3) for a total dose of 25 mg chloroquine base/kg over three days with a maximum total of 1,500 mg chloroquine base (maximum of 2,500 mg chloroquine phosphate salt) over three days in three divided doses [19].

Although CQ has been the cheapest and mainstay, treatment for vivax, malaria in Ethiopia, its efficacy is not well established, throughout the country. There is, little information on the response of *P. vivax* to CQ in Ethiopia. To mention them, a study conducted from Debre Zeit area in 1996, the rate of parasitological failure to CQ treatment on day 7was indicated to be 2% (n = 255)[20] and more recently an increased overall failure rate of 5.76% at same area[21]. Such growing evidences of the occurrence of CQR at varying degrees in Ethiopia necessitate further regular assessment of the drug’s treatment outcome in different setting to help support policy makers if changes in treatment policies are to be made. Therefore, in the present study, we planned to assess the efficacy of standard CQ treatment for *P. vivax* malaria in a one arm observational, prospective follow up study among patients who will be visiting the outpatient department of Bullen Health Center, Northern, Ethiopia.

**Significance of the study**

Antimalarial Drug resistance is a problem that contributes an estimated 90% of the malaria burden out of the total cases. So, in vivo test of CQ efficacy in Metekel, Bullen district, one of malaria endemic areas in Ethiopia, based on WHO protocol, will be benchmark for further study and it gives a clue on the current situation of CQ affectivity. Therefore conducting a study in this area brings the problem in to light; is one of the means to formulate recommendations and to assist the regional ministry of health making informed decisions on current national antimalar­ial treatment guidelines, particularly of vivax malaria.

**Methods**

**Study area**

The BFGS has an estimated area of 51,000 square kilometers and shares common borders with the State of Amhara in the east, the Sudan in the north-east, and the State of Oromia in the south. It is divided into 3 administrative zones, 19 Weredas and 33 Kebeles (the smallest administrative units) [22].  Metekel is the largest zone with an area of 26,272 square kilometers followed by Assosa and Kamashi. The state has diverse topography and climate. The later includes the familiar traditional zones - "kola", "dega", and "woyna dega". "About 75% of the State is classified as "kola" (law lands) which is below 1500 meters above sea level. The altitude ranges from 550 to 2,500 meters above sea level. The average annual temperature reaches from 20-250C. During the hottest months (January - May) it reaches a 28 - 340C. Bullen is one of the town in the Metekel zone of BGRS which lies on a longitude of 10°0o0°N 39°590 E36°0'0"E and latitude of 12°0'0"N. The town has a total of 30,828 inhabitants, and malaria is implicated to be one of the major health problem in the area [23].

**Fig 1**. Map of study site

**Population**

**Source population**

Patients who are 6 months old and visiting Bullen health center from July to December, 2014 in Bullen district will be considered as the source population.

**Study population**

Patients attending the health center with symptoms suggestive of malaria, are the study population.

**Study subject**

People who are *plasmodium vivax* mono infected and 6 months old and fulfills the inclusion criteria of WHO will be enrolled for quantitative study. All adult patients will sign an informed consent form for participation. Parents or guardians will give informed consent on behalf of children in age of less than 18 years.

**Inclusion and exclusion criteria**

Patients will be selected on the basis of the following WHO criteria:

- Patients 6 months and above
- Absence of severe malnutrition characterized by standard of WHO protocol
- A slide-confirmed infection with *P.vivax* only (i.e. no mixed infections).
- Initial parasite densities greater than 250 asexual parasites/μl
- Patients with no other signs of severe and complicated malaria according to current WHO definitions
- Having the measured axillary temperature 37.5 °C
- Ability to attend the stipulated follow-up visits, and easy access to the health facility.
- Informed consent provided by patient or parent/guardian
- ability to swallow oral medication;
- absence of concomitant febrile diseases
- absences of history of allergic reaction to CQ treatment
- ability and willingness to comply with the protocol for the duration of the study and to comply with the study visit schedule;

Individuals who did not fulfill the above criteria and the followings will not include:

- Study subjects who are Pregnant or lactating or
- The existences of underlying chronic severe illness (e.g. cardiac, renal, hepatic diseases, HIV/AIDS) will not consider as study subjects.

**Loss to follow-up**

Loss to follow-up will be deemed to occurs when, despite all reasonable efforts, an enrolled patient does not attend the scheduled visits and cannot be found. No treat­ment outcome will be assigned to these patients. Every effort will made to schedule a follow-up visit for patients who fail to return to the study site, especially during but also after administration of the drug. These patients will be classified as lost to follow-up and censored or excluded from the analysis. Patients who are lost to follow-up but who subsequently return to the study site before day 28 will not be turned away and will be encouraged to return for check-up visits.

**Protocol violation and withdrawn**

Study patients who meet any of the following criteria will be classified as withdrawn.

- Withdrawal of consent, a patient may withdraw consent at any time, without prejudice for further follow-up or treatment at the study site.
- A patient who vomits the study medication twice will be withdrawn from the study and given rescue treatment.
- failure to attend the scheduled visits during the first 3 days
- Serious adverse events necessitating termination of treatment before the full course is completed.
- Severe malaria on day 0
- if self-or third-party administration of anti­malarial drug (or antibiotics with antimalarial activity)
- Occurrence during follow-up of concomitant disease that would inter­fere with a clear classification of the treatment outcome;
- Detection of a mono-infection with another malaria species during follow-up
- Misclassification of a patient due to a laboratory error (parasitaemia), leading to administration of rescue treatment

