**Specific objectives**

- To assess the clinical efficacy of CQ among  6 months old who suffer from uncomplicated vivax malaria
- To measure the parasitological efficacy of CQ among 6 months who suffer from uncomplicated vivax malaria; and
- To assess the incidence of adverse events in vivax malaria mono infected patients who take CQ treatment

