**Measurements**

**Variables**

**Dependant variables**

- A 28 days of CQ efficacy/clinical and parasitological outcome after treatment through the following methods:
- **Hemoglobin concentration:** Hemoglobin will be determined through Hem cue heamatological analyzer or through haematocrit at days of 0, and 28 of time schedule to check the improvement of the patients’ heamoglobine level, which indicates indirect evaluation of the drug efficacy.
- **Clinical signs and symptom consideration:** the clinical outcome of patients after treatment will be assessed and recorded according to the protocol of WHO (2009).
- **Parasitic loads:** Parasitic load will be quantitate according to the schedule of WHO protocol (day 0, 1, 2, 3, 7, 14, 21and 28 day), and will help for the classification of the drug response.
- Early Treatment Failure (ETF)
- Late Clinical Failure (LCF)
- Late Parasitogical Failure (LPF)
- Adequate Clinical and Parasitological Response (ACPR)
- **Time to fever clearance (FCT)**: Time to fever clearance will be record according to the WHO protocol.
- **Safety and tolerability**: The incidence of any adverse event will be documented. All patients will be asked routinely about previous symptoms and about symptoms that have emerged since the previous follow-up visit through checklists. When clinically indicated, patients will be evaluated and treated appropriately. All adverse events will be recorded on the case report form.

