**Quality control**

Clinical examination and parasite counts will be perform every day for two consecutive days whether the parasites and symptoms are completely cleared or not and continuous check up will be perform weekly from day 7 of the first drug administration till 28 days of total follow up days. Axillary temperatures will record every day of the first two days during blood sample collection. Primary end points of the study are the parasitological and clinical response to treatment. All slides on day 0, all positive slides after day 7 (regardless of the parasite species) and 10% randomly selected negative slides will crosschecked by a senior laboratory technician who are engaged in the regional laboratory. The machine that can measure heamoglobin will be calibrated and adjust through standards and, reagents like Giemsa stains will be check by the known positive samples. In addition, for the laboratory technicians, if necessary refreshment course on the identification and enumeration of the parasites will be provide.

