**Adequate Clinical and Parasitological Response(ACPR)**

Absence of parasitaemia on Day 28 irrespective of axillary temperature without previously meeting any of the criteria of Early Treatment Failureor Late Clinical or Failure or Late Parasitological Failure is taking as ACPR.

**Time to fever clearance (FCT)**: Time to fever clearance is define as time from first dose until the first time the body temperature decreased below and remained below 37.5° C for at least a further 48 hours.

**Safety and tolerability -** The incidence of any adverse event will be documented. All patients will be asked routinely about previous symptoms and about symptoms that have emerged since the previous follow-up visit. When clinically indicated, patients will be evaluated and treated appropriately.

**Parasite clearance time**- defined as the first thick film negative for two consecutive days and

**Fever clearance time** - axillary temperature below 37.50C for two consecutive days

**Sever malaria:** Severe manifestation of malaria in adults and children will be considered through Clinical manifestations and Laboratory findings.When a patient manifest Prostration, impaired consciousness, respiratory distress, multiple convulsions, circulatory collapse, pulmonary edema, abnormal bleeding, jaundice and haemoglobinurea clinically moreover, laboratory results helps to confirm the disease severity. Findings which help for classification of Severe malaria includes sever anaemia having haemoglobin level of < 5 g/dl or haematocrit < 15%. In addition, hypoglycemia with blood glucose level < 2.2 mmol/l or 40 mg/dl, acidosis (plasma bicarbonate < 15 mmol/l), hyperlactataemia (venous lactic acid > 5 mmol/l), hyperparasitaemia (>4% in non-immune patients), renal impairment (serum creatinine above normal range for age) and among childrenthe occurrence oftwo or more convulsions within 24 h and persistent vomiting will be considered as sever malaria infection.

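### The double-vomiting rule withdraws the patient from the whole study, so safety observation ends along with efficacy classification

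*Protocol*

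**What the plan says.** The section Protocol violation and withdrawn opens with "Study patients who meet any of the following criteria will be classified as withdrawn". Two items in its list concern tolerability. The first is an instruction on conduct: "A patient who vomits the study medication twice will be withdrawn from the study and given rescue treatment". The second is only a ground for classification: "Serious adverse events necessitating termination of treatment before the full course is completed".

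Safety is part of the general objective, and one specific objective is "To assess the incidence of adverse events in vivax malaria mono infected patients who take CQ treatment". On how events are found, the safety entry under Dependant variables says "All patients will be asked routinely about previous symptoms and about symptoms that have emerged since the previous follow-up visit through checklists" and then "All adverse events will be recorded on the case report form". The operational definitions repeat that "The incidence of any adverse event will be documented". Both places add that patients are assessed and treated where there is a clinical reason.

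The Abstract schedules evaluations on Days 1, 2, 3, 7, 14, 21 and 28. Under Quality control, "Primary end points of the study are the parasitological and clinical response to treatment".

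**The concern.** Repeated vomiting of the dose is a sound reason to stop study treatment, give rescue treatment and assign no efficacy outcome. It is not a reason to stop asking about adverse events. The rule as worded does both, because it removes the patient from the study without qualification.

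The patients removed have just shown intolerance of the drug whose adverse events the study sets out to count. Later events that go unobserved cannot be recovered by any analysis, so this is a matter for the protocol rather than for a statistical analysis plan. At stake are later events in this group, and hence counts and proportions for particular event types.

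**Working it through.** The plan gives no figure on this point to reproduce. The check sets the relevant sections side by side and then sizes the loss per patient.

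**Does the text end safety observation for double vomiters?**

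1. The vomiting rule withdraws the patient from the study as a whole. It contains no clause confining this to efficacy.
2. The adverse-event questioning asks what has emerged since the last follow-up visit. It therefore works only while visits continue.
3. The only express invitation to keep attending is under Loss to follow-up, for patients who were lost and come back before Day 28. The item on withdrawn consent protects further follow-up or treatment at the site, but for those patients only. Neither covers double vomiters.
4. Read literally, scheduled safety observation therefore stops at the second vomit. The vomiting itself is still recordable, because all adverse events go on the case report form.

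**Does the same hold for treatment-ending serious adverse events?** Not on the text. That item is a ground for classification and says nothing about leaving the study or ending visits.

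**Visits lost per double vomiter.** Inputs: the seven post-baseline visits in the Abstract, three daily doses (Introduction), and follow-up counted from Day 0 (Dependant variables and the early treatment failure definition). Doses then fall on Days 0, 1 and 2. Days lost are 28 minus the day of withdrawal.

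| Withdrawn at | Study day | Visits left | Share of 7 | Days left of 28 |
|---|---|---|---|---|
| Dose 1 | 0 | 7 | 100% | 28 |
| Dose 2 | 1 | 6 | 6/7 = 86% | 27 |
| Dose 3 | 2 | 5 | 5/7 = 71% | 26 |

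The Introduction numbers the doses as Days 1 to 3, but as treatment days in the national dosing guidance. The study's own follow-up starts at Day 0.

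**Effect on the results.**

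- Proportion with any adverse event: change of 0, provided the vomiting is counted, since the patient already has an event.
- Proportion with one particular later event: each patient whose event is missed lowers it by 1/422 = 0.24 percentage points (1/384 = 0.26 on the uninflated sample size). This is simply one patient's weight.
- Scale, on assumptions that are not in the documents: let w be the fraction withdrawn under the rule, b the rate of later events in other patients, and r the ratio of the rate in withdrawn patients to b. If withdrawn patients stay in the denominator with no later events recorded, the shortfall is w × r × b. With w = 1%, r = 1 and b = 5% it is 0.01 × 1 × 0.05 = 0.05 percentage points. With w = 5%, r = 4 and b = 10% it is 0.05 × 4 × 0.10 = 2.0 points. Over w = 1% to 5%, the patients affected number 422 × 0.01 = 4 to 422 × 0.05 = 21.

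**The case against.** The strongest reply is that the protocol already promises to document every adverse event, to question all patients, and to assess and treat them where clinically needed. On that view withdrawal is only an outcome label. Loss to follow-up supports this: those patients are classified and censored or excluded, yet still encouraged to return.

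For serious adverse events this reply largely succeeds. A reader might infer that the outcome of a treatment-ending serious event is lost, but the documents do not support that. The text only classifies the patient, does not say visits stop, and provides for clinical assessment and for recording of all events. What remains is unclear wording.

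For double vomiters the reply fails. Their item goes beyond classification and takes them out of the study. The general promises are carried out through visits that the rule, read literally, ends.

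Two further objections stand in part. Double vomiters go straight to rescue treatment and may have retained little chloroquine, so later events say less about chloroquine alone. And the annexed exclusion criteria already screen out repeated vomiting and known intolerance, which should keep the group small. Both limit the value of the lost data without making the rule right.

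**Conclusion.** The point holds for patients who vomit the study medication twice. Followed literally, the rule ends their safety observation, at a cost of 5 to 7 of 7 post-baseline visits per affected patient. This assumes dosing from Day 0 and that staff apply the words as written. The number of such patients is unknown and likely small, and the shortfalls of 0.05 to 2.0 percentage points rest wholly on assumed rates.

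A reader might also infer that the safety objective fails or that the efficacy result is distorted. Neither follows. The triggering event is recorded, the proportion with any adverse event need not move, and the primary endpoint is parasitological and clinical response. The effect is confined to later events in a few patients. For treatment-ending serious adverse events the conclusion is only that the wording is ambiguous. Overall this is an optional, low-cost improvement.

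**What to change.** Replace the vomiting item in Protocol violation and withdrawn with wording such as: a patient who vomits the study medication twice is withdrawn from study treatment and from efficacy classification only, is given rescue treatment with the drug and its date recorded, and is asked to attend the remaining scheduled visits to Day 28 for adverse-event recording. Add that the same applies after a serious adverse event that ends treatment, which removes the ambiguity there.

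The cost is a wording change, one extra data item for the rescue drug and its date, and for a double vomiter 5 to 7 visits that are already planned for every enrolled patient. The drawback is that events after rescue treatment can be attributed to chloroquine only to a limited degree; the recorded date lets them be identified. The denominator and the display of such events can be left to the statistical analysis plan.
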